### Secondary Research Objectives

The **s**econdary research objectives were as follows:

Establish the participants’ expectancy toward both interventions.Examine the participants’ satisfaction with the interventions.Generate estimates to inform sample size calculations for a future multicenter RCT.Assess whether there is preliminary evidence of an efficacy signal for QoL, fatigue, symptoms, resiliency, self-efficacy, cognition, anxiety, depression, and mindfulness.Examine the experimental group’s baseline characteristics, adherence, and attrition rates in those who chose to continue for an additional 4 weeks compared with those who chose to complete the study at 4 weeks compared with those who were lost to follow-up.Examine the control group’s baseline characteristics, adherence, and attrition rates in those who chose to cross over to the experimental interventions at 4 weeks versus those who chose to complete the study at 4 week versus those who were lost to follow-up.Examine whether the experimental intervention is associated with differential brain-based imaging patterns of functional connectivity, cerebral blood flow, and spectroscopy.Examine safety by examining whether the experimental intervention has increased adverse events (ie, total number) relative to the control intervention.

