## Methods

### Trial Design

The proposed study is a Health Canada–regulated parallel-group (1:1) RCT, where patients within 7 days of a concussion will be randomly assigned to one of the two groups: (1) experimental group (n=35), early introduction of the DTx MBI program and (2) control group (n=35), sham DTx attention-matched comparator intervention. The participants will start the intervention the next day after being enrolled in the study. After 4 weeks, those in the experimental group will be offered the MBI program with 4-week additional education modules. Those who are part of the control group will be offered to cross over to start the DTx MBI. Of the 70 participants enrolled, 60 (86%) consenting participants (n=30, 50% from the experimental group and n=30, 50% from the control group) will be enrolled in neuroimaging, which requires participation in a brain scanning session within 72 hours of enrollment and during week 4 of the study. For a schematic diagram of the trial design, procedures, and stages, refer to the study flow diagram in Figure 1.

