##### Safety

*Safety* of the MBI will be determined by capturing and monitoring the worsening of symptoms and adverse events. Adverse events will be defined as an unscheduled visit to the ED or primary medical provider because of exacerbation of symptoms during or within 30 minutes after using the app. The participant will be asked about any possible adverse events at the 1-, 2-, 4-, and 8-week follow-ups.

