#### Statistical Power

##### Feasibility Objective

The sample size calculations were informed on recommendations for feasibility trials using the *traffic light* system [50,89]. The significance cutoff points for each criterion, with green lower and red upper limits, were determined. Using Table 1 from the study by Lewis et al [50], to meet the individual >90% power requirements for each of the five criteria we would need the following: (1) for eligibility, the number of participants to be screened is 46; (2) for recruitment, the number of participants to be randomized is 54; (3) for adherence, the required number of participants to evaluate adherence is 55; (4) for credibility, the required number of participants is 55; and (5) for retention, the required number of participants is 34. To determine the overall sample size for the whole study, we based our decision on the criterion that requires the largest numbers (ie, adherence, n=55). Considering an approximately 20% rate of loss to follow-up and withdrawals, the required sample size for the adherence criteria is 70. We expect that 40% of the participants screened will be eligible and there will be a 50% recruitment uptake. Given these numbers, 350 children are expected to be screened: 350=[(1/0.4)×(1/0.5×70)]. Assuming that 70 of the 350 screened participants are randomized, criteria 1, 2, 3, 4, and 5 will have statistical powers of 100%, 99.9%, 95.8%, 95.8%, and 98.7%, respectively. This means that the null hypotheses can be rejected with a collective power of 90.5% if the alternative hypotheses (for acceptable feasibility outcomes) are true in each case.

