#### Potential Harms

The safety outcomes include (1) severe worsening of symptoms identified on HBI reliable changes or (2) any symptoms requiring an unscheduled visit to the ED or primary care provider. If concussion symptoms worsen during the treatment to the degree that the participant requires an unscheduled visit to the ED or primary care provider, then symptoms will be considered as a possible adverse event. Symptoms could develop into an adverse event if they become unbearable and the patient needs immediate medical attention. Patients will report possible adverse events through REDCap reports, and their responses will be monitored by RAs. In the case of a possible adverse event, defined as the *worsening of symptoms requiring an unscheduled visit to the ED or primary care provider*, site investigators will be notified to determine if the event is linked to the treatment. If linked, the event will be monitored and the CHEO Research Ethics Board and DSMB will be notified.

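### The between-arm safety comparison counts adverse-event visits rather than participants affected, so repeat visits by one or two adolescents can distort it

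*Protocol article*

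**What the plan says.** Under Secondary Research Objectives, the protocol article names the measure for the safety comparison: "Examine safety by examining whether the experimental intervention has increased adverse events (ie, total number) relative to the control intervention". The parenthesis fixes the unit as the event.

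The Safety section defines that unit: "Adverse events will be defined as an unscheduled visit to the ED or primary medical provider because of exacerbation of symptoms", limited to exacerbations that occur while the app is in use or in the half hour afterwards. It also sets the occasions for asking: "The participant will be asked about any possible adverse events at the 1-, 2-, 4-, and 8-week follow-ups". Nothing limits a participant to one event.

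Trial Design gives the arms as "experimental group (n=35), early introduction of the DTx MBI program" and "control group (n=35), sham DTx attention-matched comparator intervention".

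Potential Harms widens the list of safety outcomes: "The safety outcomes include (1) severe worsening of symptoms identified on HBI reliable changes or (2) any symptoms requiring an unscheduled visit". It states no between-arm comparison for the symptom-worsening item. The Statistical Analysis section gives no safety test, significance level or model. Nowhere does the article mention the number or proportion of participants with at least one adverse event.

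**The concern.** Participants are randomised, but the objective counts visits. An adolescent whose symptoms flare when using the app is exposed to it again and again, because the intervention description encourages use on at least four days a week. Such a participant may return more than once, and a single flare may lead to both a primary-care and an emergency visit.

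The arm total therefore mixes two quantities: how many participants were harmed, and how often those few came back. When events are sparse, the second can dominate. At stake is the reading of the only between-arm safety comparison that the article states, in a trial meant to inform a larger multicentre one. An apparent excess in the mindfulness arm, or its absence, could reflect the behaviour of one or two people.

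**Working it through.** **The plan's own figure.** The article gives no adverse-event rate, repeat-visit rate or safety power, so there is no safety figure to reproduce. The arm size can be checked. The Feasibility Objective section says "Considering an approximately 20% rate of loss to follow-up and withdrawals, the required sample size for the adherence criteria is 70", starting from 55: 55 / (1 − 0.20) = 68.75, so 69. The stated 70 agrees within rounding and gives 35 per arm.

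**Worked counts at 35 per arm.** Events in an arm = participants affected + extra visits. A participant with four visits adds three extra. The p-values only gauge how large the imbalance looks; the article plans neither test.

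| Case | Participants affected (mindfulness v control) | Repeat visits assumed | Visits | Fisher p, participants | Exact binomial p, visits treated as independent |
|---|---|---|---|---|---|
| Apparent harm | 3 v 3 | one mindfulness participant with 4 | 3 + 3 = 6 v 3 | 1.0 | 0.51 |
| Apparent harm | 3 v 3 | two mindfulness participants with 4 each | 3 + 6 = 9 v 3 | 1.0 | 0.15 |
| Hidden difference | 6 v 3 | one control with 4 | 6 v 3 + 3 = 6 | 0.48 | 1.0 |
| Hidden difference | 8 v 2 | both controls with 4 each | 8 v 2 + 6 = 8 | 0.08 | 1.0 |

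The 0.15 is 2 × (1 + 12 + 66 + 220) / 4096 = 598 / 4096.

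**Added noise, under assumptions.** Let a proportion p of each arm be affected. Let a fraction q of those make four visits and the rest one. For visits V per affected participant, E(V) = 1 + 3q and E(V²) = 1 + 15q. The SD of the arm difference is √{2 × 35 × [p·E(V²) − p²·E(V)²]} for visits and √{2 × 35 × p(1 − p)} for participants.

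With p = 0.10 and q = 0.20, E(V) = 1.6 and E(V²) = 4.0.
- Visits: √{70 × (0.40 − 0.0256)} = √26.2 = 5.12.
- Participants: √{70 × 0.09} = √6.3 = 2.51.
- Ratio: 2.04.

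Across p of 5%, 10% and 20% and q of 20% and 40%, the ratio runs from about 2.0 to 2.8. Part of that is scale, because totals are larger numbers. Dividing by E(V), for example 2.04 / 1.6 = 1.27, leaves about 1.2 to 1.3 times the noise relative to the mean.

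**How often a striking imbalance arises by chance.** In a simulation with no true difference (100,000 runs per setting), an imbalance was called striking if one arm had at least twice the other's count and at least three more.

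| Affected | Participants | Visits, q = 20% to 40% |
|---|---|---|
| 5% | 16% | 43% to 54% |
| 10% | 29% | 49% to 50% |
| 20% | 21% | 30% to 33% |

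The at-least-three-more condition is easier to meet with larger totals, so this contrast also contains a scale effect. With q = 0 the two columns coincide.

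**Only if totals were tested as independent events.** In the same simulation, such a test at 5% rejects in 9% to 21% of trials when visits repeat and in 0.3% to 1.4% when they do not. Fisher's test on participants rejects in 0.3% to 2.5%.

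**The case against.** The strongest reply is that the article describes no safety test, so nothing in it has an error rate to inflate. That stands. A reader might infer that the plan carries a false-signal rate well above 5%. The documents do not support this: such rates belong to a test that treats visits as independent, and the plan does not contain that test. A reader might also infer that the total often points in the wrong direction. In the simulation, visits and participants favoured opposite arms in 6% to 14% of trials, but the arms were identical, so no true direction existed to get wrong.

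Second, the app-time window in the Safety section narrows what counts, and the Data Safety Monitoring Board section calls the intervention low risk. Repeat visits may therefore be rare. This also stands: the assumed rates have no support in the documents. A dramatic example such as 12 v 3 visits from 3 v 3 participants (p = 0.035 on independent visits) needs an average of four visits per affected mindfulness participant, and the milder 9 v 3 is not significant even on that naive test.

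Third, safety is not among the progression criteria in Table 2, site investigators assess whether possible events are linked to treatment, and the monitoring board can meet early. This limits the consequence, but none of it alters the reported arm comparison. Symptom worsening on the Health and Behavior Inventory is a participant-level outcome, but it has no stated arm comparison.

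Fourth, a condensed article may leave adverse-event tables to fuller documents, and total events is a legitimate measure of burden. True, but here the article names the measure, so an analysis plan that follows the objective would inherit it.

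**Conclusion.** The point holds as a weakness in a descriptive comparison. The article fixes total events as the between-arm safety measure and defines an event so that one participant can supply several. At 35 per arm, 3 v 3 participants affected can appear as 9 v 3 visits, and 6 v 3 as 6 v 6, through repeat visits by one or two people.

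The size in practice is unknown. It depends on event and repeat-visit rates that the article does not give, and it is zero if nobody makes a second visit. Inflated error rates would arise only if totals were tested as though visits were independent. Since safety is a secondary objective of a feasibility trial and individual events are reviewed separately, this is a worthwhile and inexpensive improvement, not a flaw that threatens the trial.

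**What to change.** Reword the safety objective so that the main comparison is the number and percentage of randomised participants in each arm with at least one adverse event, with an exact confidence interval per arm and a confidence interval for the risk difference. Report the total number of events beside it as a supporting description. If totals are tested, use a method that allows for repeat events within a participant, such as a negative binomial model or a participant-level bootstrap.

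The cost is one objective and one table. Participants are asked about events individually at each follow-up, so no new data are needed.

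There are two downsides. Repeat visits carry less weight in the main comparison, though they stay visible in the total. The participant-level comparison also remains imprecise: 3 of 35 is 8.6%, with an exact (Clopper-Pearson) 95% interval of 1.8% to 23.1%, and 6 of 35 is 17.1%, with 6.6% to 33.6%. The change makes the comparison interpretable but does not make it powerful.

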## Methods

### Trial Design

The proposed study is a Health Canada–regulated parallel-group (1:1) RCT, where patients within 7 days of a concussion will be randomly assigned to one of the two groups: (1) experimental group (n=35), early introduction of the DTx MBI program and (2) control group (n=35), sham DTx attention-matched comparator intervention. The participants will start the intervention the next day after being enrolled in the study. After 4 weeks, those in the experimental group will be offered the MBI program with 4-week additional education modules. Those who are part of the control group will be offered to cross over to start the DTx MBI. Of the 70 participants enrolled, 60 (86%) consenting participants (n=30, 50% from the experimental group and n=30, 50% from the control group) will be enrolled in neuroimaging, which requires participation in a brain scanning session within 72 hours of enrollment and during week 4 of the study. For a schematic diagram of the trial design, procedures, and stages, refer to the study flow diagram in Figure 1.

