#### Exclusion Criteria

Patients will be excluded if they present with TBIs with any of the following: (1) a Glasgow Coma Scale score of ≤13; (2) abnormality on standard neuroimaging studies [41], including positive head computed tomography findings (neuroimaging is not required, but may be performed if clinically indicated); (3) neurosurgical operative intervention, intubation, or intensive care required; (4) multisystem injuries with the treatment requiring hospital admission, operating room, or procedural sedation in ED (hospital admission for observation or management of ongoing concussion symptoms is not an exclusion criteria); (5) severe chronic neurological developmental delay resulting in communication difficulties; (6) intoxication to alcohol or drugs at the time of ED presentation as per clinician judgment; (7) no clear history of trauma as primary event to the concussion (eg, seizure, syncope, and migraine); (8) prior psychiatric hospitalization; (9) inability to obtain written informed consent or assent (eg, language barrier); (10) legal guardian not present (certain forms need to be completed by parents or legal guardians); (11) no internet and mobile or tablet access; and (12) currently in therapy.

In addition, patients will not be included in the magnetic resonance imaging (MRI) component if they present with the following: (1) previous neurological or neurodevelopmental disorder such as epilepsy, intellectual disability, or autism (history of attention-deficit or hyperactivity disorder or learning disability is not exclusionary); (2) previous stroke or transient ischemic attacks; (3) sedation medication (eg, propofol, ketamine, nitrous oxide, midazolam, benzodiazepines, and fentanyl) administered before or during ED visit; (4) inability to be present at the 72-hour (+48 or –48 hours) and 4-week (+5 or –5 days) MRI follow-up visits; and (5) medical contraindications to MRI (eg, claustrophobia, pregnancy, or presence of braces or spacers or other metal implants).

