##### Sample Size for the Nested Neuroimaging Component

As per Desmond and Glover [90], a liberal threshold of α=.05 requires 24 participants (12 per group) to achieve an 80% power for the single-voxel level for typical activations. To control the error rate when conducting multiple comparisons, it is suggested that the number of participants should be doubled to maintain this level of power. On the basis of our Pediatric Concussion Assessment of Rest and Exertion and MRI study, of the 89 participants with concussion who provided consent, 13 were lost to follow-up, 3 had incidental findings, and 5 had excessive motion [91]. Considering a 20% attrition, a total sample size of 60 participants (30 per group) will be recruited.

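### Taking 60 imaging participants from 70 leaves a thin, unlabelled margin for MRI exclusions and refusals, and even a full 60 does not secure the 48 analysable behind the 80% power statement

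*Protocol article*

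**What the plan says.** All references are to the protocol article.

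- **Trial Design** takes the imaging sample from inside the trial: "Of the 70 participants enrolled, 60 (86%) consenting participants", split as "n=30, 50% from the experimental group and n=30, 50% from the control group) will be enrolled in neuroimaging". Neuroimaging Procedures repeats 60, 30 from each group.
- **Sample Size for the Nested Neuroimaging Component** starts from a cited source that "requires 24 participants (12 per group) to achieve an 80% power for the single-voxel level for typical activations". It adds that, to allow for multiple comparisons, "it is suggested that the number of participants should be doubled to maintain this level of power". It then reports the earlier imaging study, where "of the 89 participants with concussion who provided consent, 13 were lost to follow-up, 3 had incidental findings, and 5 had excessive motion", and concludes: "Considering a 20% attrition, a total sample size of 60 participants (30 per group) will be recruited".
- **Exclusion Criteria** lists five exclusions that apply to the MRI component only: neurological or neurodevelopmental history, previous stroke or transient ischemic attack, sedation medication, inability to attend both scan visits, and "medical contraindications to MRI (eg, claustrophobia, pregnancy, or presence of braces or spacers or other metal implants". MRI also needs the participant's separate agreement (Data Collection Methods).
- **Feasibility Objective** sets the total of 70 from the adherence criterion alone: 55 inflated for about 20% loss.
- **Neuroimaging Component: Nested Study** restricts the imaging analysis to participants who adhered to the intervention. Table 2 puts the green threshold for adherence at more than 70%.

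**The concern.** The 60 and the 70 come from two separate calculations that are not reconciled with each other. The 70 serves the adherence criterion. The 60 serves the imaging power statement and must then be found among the 70. Anyone who refuses MRI or is ineligible for it has to fit into the 10 places between the two numbers, and the article does not describe those places as an allowance for anything.

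The attrition step has a second weakness. The losses cited in its support all occurred after consent, and together they exceed the 20% used. The restriction to adherent participants does not enter the calculation at all.

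At stake is whether the imaging comparison can be described as sized for 80% power. If the analysable number falls well below the one behind that statement, the statement describes a property the design does not have.

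**Working it through.** **1. Reproduce the plan's figure.** 24 participants doubled is 48. Inflated for 20% attrition, 48 / (1 − 0.20) = 60, which matches. The 48 is implied and is not printed in the article. The base of 24 comes from a cited source and is taken as given.

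**2. Margin before imaging starts.** 60 / 70 = 85.7%, so refusals and MRI-only exclusions together may remove at most 10 of 70 (14.3%).

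**3. Chance of reaching 60.** Let *u* be the proportion of enrolled participants who are both MRI-eligible and willing. The article gives no value, so *u* is an assumption shown over a range. The number available is taken as binomial (70, *u*), with P(at least 60) from the exact tail.

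**4. Loss after consent.** The earlier study lost 13 + 3 + 5 = 21 of 89 = 23.6%, assuming the three groups do not overlap. From a full 60, 60 × 68/89 = 45.8 remain. To retain 48 at that rate, 48 / (68/89) = 62.8, so 63 would have to be recruited.

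**5. Adherent-only analysis.** With 20% loss and 70% adherence treated as independent, 60 × 0.8 × 0.7 = 33.6. Independence is an assumption. In the most favourable case, where everyone lost is also non-adherent, the ceiling at 70% adherence is 60 × 0.7 = 42, still below 48.

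**6. Together, for 70 enrolled:**

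| Assumed uptake *u* | Expected in imaging (70*u*) | P(at least 60) | Left after 20% loss | Left after 23.6% loss | Adherent at 70%, after 20% loss | Adherent at 70%, after 23.6% loss |
|---|---|---|---|---|---|---|
| 90% | 63 | 0.91 | 50.4 | 48.1 | 35.3 | 33.7 |
| 85.7% | 60 | 0.58 | 48.0 | 45.8 | 33.6 | 32.1 |
| 80% | 56 | 0.15 | 44.8 | 42.8 | 31.4 | 30.0 |
| 70% | 49 | 0.002 | 39.2 | 37.4 | 27.4 | 26.2 |

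The last column is 70*u* × 68/89 × 0.7. The 90% row assumes that all 63 would be scanned. If imaging stops at 60, the expected counts in the 85.7% row are the ceiling.

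Before any adherence restriction, the chance of at least 48 analysable after 20% loss (binomial, 70 and 0.8*u*) is 0.78 at 90% uptake, 0.25 at 80% and 0.02 at 70%.

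**The case against.** **The 10 spare places are an allowance, and 86% may be achievable.** This largely stands. The 70 have already agreed to research, and at 90% uptake the chance of reaching 60 is 0.91. A reader might infer that the article shows 60 to be out of reach. It does not: without an MRI uptake rate, the shortfall is likely at about 80% or below and unlikely at about 90% or above. What can be said is that the margin is unlabelled and thin.

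**Main-trial uptake.** A reader might take "We expect that 40% of the participants screened will be eligible and there will be a 50% recruitment uptake" as a guide and expect about half to accept MRI. The comparison is not like for like. That rate describes eligible patients approached for the trial, whereas MRI uptake is conditional on having already enrolled.

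**Both arms at 30.** One could require at least 30 of 35 in each arm, which has a chance of only 0.38 at 86% uptake. That test is too strict. A split of 31 and 29 would barely affect the planned regression, so the total is the relevant count. A target equal to its expected value is also missed about half the time in any design.

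**Detectable differences.** It is tempting to attach a smallest detectable effect to each analysable number. The article does not allow it: the doubling to 48 is for multiple comparisons, and neither the effect size nor the corrected threshold is given. A figure at an uncorrected 5% would not belong to this design.

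**Condensed article, exploratory component.** The full protocol may contain an uptake projection, so its absence here is not the point. Imaging is one of eight secondary objectives and is described as preliminary, which limits the severity. But the article does state a fixed count and a power basis, and its own loss figures and analysis set do not support them.

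**Conclusion.** The point holds in a limited form. The arithmetic giving 60 is correct. Whether 60 can be drawn from 70 is open, because it depends on an MRI uptake that the article does not give.

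The firmer part does not depend on uptake. With all 60 places filled, the earlier study's loss rate leaves about 46 analysable, and the adherent-only analysis leaves about 34 at 20% loss and 70% adherence, against the 48 implied by the power statement. The 46 assumes that the earlier losses do not overlap and carry over to this trial. The 34 assumes independence of loss and adherence, and adherence at the green threshold rather than above it.

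The size behind the 80% power statement is therefore not secured. The consequence is confined to a secondary, preliminary component. The feasibility outcomes and the progression decision are untouched.

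**What to change.** 1. In Trial Design, Neuroimaging Procedures and the imaging sample-size section, replace the fixed 60 (30 per group) with *up to 60*. Carry the change to the other places that repeat the number (Abstract, Table 3, Imaging Measurements).
2. In the imaging sample-size section, state the expected scanned and analysable numbers over a range of MRI uptake labelled as assumed, for example 70% to 90%. Use the 23.6% loss from the earlier study and show the effect of the adherent-only restriction. The table above supplies the figures.
3. Remove the 80% power statement, or qualify it as applying only if 48 participants are analysable under the planned analysis set. Present the imaging contrast as preliminary estimates with confidence intervals.

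Do not enrol more patients for this purpose. The cost is wording and a less favourable statement of the imaging precision; no extra participants or scans are involved.
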